**Secondary outcomes**		
Medical appointment-keeping	Medical record data and self-reported survey data	Study generated
Substance Use (reduction or abstinence for 7 + days)	NIDA-Modified ASSIST V2.0 [54] Biomarkers: urinary drug assessments of fentanyl, opioids, and other drugs (i, e., methamphetamines, cocaine, MDMA, other opioids)	http://www.sbirtoregon.org/wpcontent/uploads/Modified-ASSIST-English-pdf.pdf https://nida.nih.gov/sites/default/files/pdf/nmassist.pdf
Alcohol Use	AUDIT-C [55]	https://cde.nlm.nih.gov/formView?tinyId=myWNfJaZwe
Motivation (e.g., to stop using opioids, to take buprenorphine)	Readiness Ruler [56]	https://case.edu/socialwork/centerforebp/resources/readiness-ruler
Depression and Anxiety	PHQ-4 [57]	https://www.oregonpainguidance.org/app/content/uploads/2016/05/PHQ-4.pdf
Childhood Trauma Experiences	ACES [58]	https://www.acesaware.org/wp-content/uploads/2022/07/ACE-Questionnaire-for-Adults-Identified-English-rev.7.26.22.pdf
Social Support	MOS Social Support Survey [58], [59], [60]	https://pubmed.ncbi.nlm.nih.gov/2035047/
Experience with Technology	Adapted from Garfein, et al. VDOT study [60]	Garfein, et al. (2018). Tuberculosis Treatment Monitoring by Video Directly Observed Therapy in 5 Health Districts, California, USA. *Emerging infectious diseases*, *24*(10), 1806–1815. 10.3201/eid2410.180459
Library Usage	Questions around individuals use of the library (e.g., time spent visiting, activities at library, frequency of visits)	Study generated
OUD Treatment Histories	Questions eliciting information on prior pharmacological or psychological treatment of opioid use disorder (e.g., methadone, counseling)	Study generated

At the end of the participants’ 12-week participation in the study, research staff interview participants about their experience with library telehealth and the acceptability of BBB study participation. To avoid potentially biased responses, interviews are conducted with study staff not involved in the person’s care. All participants in the library-facilitated telehealth and control groups complete a post-treatment satisfaction survey regardless of whether or not they sustain in treatment. Data are used to assess participant satisfaction and identify areas for improvement.

The investigators will also interview the medical providers and library staff involved in the study to get feedback about their experiences with the study protocol.

#### Data tracking and management

For tracking, the researcher assigns each participant a unique identifier number, and the study staff records and maintains each session’s date, time, and location. The researchers use the electronic tracking sheet to record drug screening results (buprenorphine, fentanyl, and other substances) collected on-site at the libraries for the research study. They also record participant receipt of incentives, study staff initials, and the type of assessment they administer (baseline or follow-up). Notes with de-identified data are also recorded in the spreadsheet.

Additionally, participant medical appointment attendance, clinic urinary drug screening outcomes, and CURES database-derived pharmacy pickup data are recorded on a separate HIPAA-compliant database to be shared only with the clinic staff on the study and selected research staff.

#### Sample size and planned data analyses

Our target sample size for the trial is 40 participants, although we allow for a maximum of 60 participants to account for attrition. The sample size will provide adequate precision for effect size estimates, though not statistically powered to assess efficacy on primary outcomes.

Buprenorphine uptake (the proportion who pick up and take buprenorphine at initiation, confirmed by CURES database pharmacy pickup records and urinary drug screenings) and adherence (taking buprenorphine > 1 time, ideally for 8 + weeks), medical appointment adherence (attended medical appointments for buprenorphine two or more times as confirmed by clinic medical record data) will be divided by the number prescribed and scheduled, respectively.

Adherence estimates from this study will also provide the basis for power calculations in the design of future efficacy trials. Quantitative data analysis will consist of univariate statistics to describe the entire study sample and by study arm, the prevalence of individual responses, and the prevalence of treatment uptake and adherence. We will conduct an intent-to-treat (i.e., per-randomization) analysis following CONSORT guidelines to explore potential differences between study arms on the outcomes. Specifically, we will use regression models testing each outcome separately (using the appropriate test depending on the outcome distribution, e.g., logistic regression with binary outcomes). These models will treat the intervention condition (library-facilitated telehealth intervention vs. treatment-as-usual control) as the exposure in unadjusted models.

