#### Feasibility of RCT to evaluate the current intervention

Rate of enrollment (Number of participants per week and per month).Proportion of interested and eligible participants who can successfully complete enrollment in the study.Study retention (proportion of RCT-enrolled participants who complete each follow-up assessment).Proportion of RCT-enrolled participants for whom outcome data are collected.We will track the proportion of participants who indicate willingness to be assigned to either condition (the percent of people who decline to participate because they do not like the randomization aspect of the study should be “none” to determine whether the study is feasible).

As a pilot study that is not statistically powered to assess efficacy, the study will provide effect size estimates of the library-facilitated telehealth BBB intervention on the primary outcomes, buprenorphine uptake and adherence, as measured by (1) presence of buprenorphine in weekly urine drug screenings at the library and at FJV health center, (2) buprenorphine prescription pick-ups, and (3) number and frequency of clinic visits, with secondary outcomes including use of fentanyl (e.g., illicitly manufactured) and other opioids (secondary outcome measured in weekly urine drug screens), and (4) self-reported substance use, mental health, and quality of life measures at 1-,2-,4-,8-, and 12-weeks, compared to a control group.

The control group will undergo the same procedures and receive the same incentives from the study staff in the library in terms of weekly assessments. They will also receive the same care from the clinic, except they will not be instructed to use the library telehealth option for their medical visits like the treatment group until their study participation is over. We hypothesize that patrons assigned to the library-facilitated telehealth group will uptake buprenorphine, pick up their buprenorphine prescriptions from the pharmacies, take buprenorphine after two weeks, and adhere to medical appointments more than the control (in-person clinic visits) group.

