Many participants feel that using the library setting for care can facilitate an added layer of discreteness for their clinical care by providing a setting to receive medication for opioid use disorder without fear of going to a clinic. Going in-person to a clinic could result in stigma from being identified as someone receiving substance disorder treatment. Further, several participants view the library as a safe location associated with reduced opportunities for encountering environmental triggers for use that may be present in a clinical setting (e.g. large waiting rooms with other individuals who also use drugs or have other mental health issues, pressure to use drugs from people congregating outside clinics for other services). The participants suggest ways to further keep participation in the study confidential at the library by using telehealth services and conducting study visits in private study rooms.

The focus groups and interviews with medical service providers and library staff helps determine ways to keep the study procedures in line with the usual clinic and library protocols to minimize the need for additional costs and staff time at either place, as well as design a protocol with a great likelihood for implementation after the study. For example, process measures are determined to be conducted by the research staff at intervals commensurate with clinical care for buprenorphine (e.g. in-between and at 1-,2-,4-,8-,12- weeks). The timeframe for determination of buprenorphine uptake outcome measures and follow-up visit schedules are vetted with the medical staff commensurate with the standard of care. The formative data gathering helps inform how we collect our process measures (e.g., meeting regularly with the health center to gather appointment keeping data). The clinic and researchers should conduct regular meetings during the duration of the study to ensure a functional and efficient trial.

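### Appointment adherence is defined by a two-visit threshold over a "scheduled" denominator, although attendance is already recorded; comparing the number of attended visits would use more of the data

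*Protocol article*

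**What the plan says.** Under Sample size and planned data analyses, the outcome is "medical appointment adherence (attended medical appointments for buprenorphine two or more times as confirmed by clinic medical record data". The same sentence adds that the outcomes it lists "will be divided by the number prescribed and scheduled, respectively", which for appointments points to the number scheduled. It does not say whether the unit is the participant or the visit. Regression models are then fitted to each outcome, "using the appropriate test depending on the outcome distribution, e.g., logistic regression with binary outcomes".

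Other sections describe the same behaviour on a fuller scale. Under Feasibility of RCT to evaluate the current intervention, the listed measures include "number and frequency of clinic visits", and the hypothesis is that the telehealth arm will "adhere to medical appointments more than the control (in-person clinic visits) group". Under Data tracking and management, "participant medical appointment attendance, clinic urinary drug screening outcomes, and CURES database-derived pharmacy pickup data are recorded".

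Table 2 lists medical appointment-keeping as a secondary outcome, although the feasibility section lists clinic visits among the measures of the primary outcomes. Under Screening and enrollment, each participant must attend one in-person clinic visit before randomisation. The analysis section does not say whether that visit counts towards the two.

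**The concern.** Library telehealth acts on follow-up visits, and the Control condition section describes it as the only difference between the arms. Appointment keeping is therefore the outcome it can most directly change, and the hypothesis is about attending more. A threshold of two cannot register any difference beyond the second visit. If the intake visit counts, it cannot register any difference beyond the first follow-up visit. No reason is given for placing the cut at two.

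The denominator does not repair this. A yes/no per person can be averaged over people, and attended visits can be averaged over scheduled visits, but a two-visit threshold divided by scheduled visits is neither.

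What is at stake is precision rather than a test result. The analysis section claims adequate precision for effect sizes and intends adherence estimates to inform power calculations for later efficacy trials. An inefficient scale weakens that use in a sample of 40.

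**Working it through.** **What can be reproduced.** The target of 40 (maximum 60) is given without alpha, power, effect size or precision target, so there is no figure to reproduce. For context, the 95% CI half-width for a difference in proportions at 20 per arm is 1.96 × √(2p(1−p)/20): 0.31 at p = 0.5 and 0.19 at p = 0.9.

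**Inputs.** From the article: 40 participants and two arms. Assumed, because the article does not state them:
- 1:1 allocation (n = 20 per arm) and two-sided 5%.
- m = 5 provider visits after randomisation. This is a proxy: the article sets research process measures "at intervals commensurate with clinical care for buprenorphine (e.g. in-between and at 1-,2-,4-,8-,12- weeks", which is not a provider schedule.
- Within-person correlation ρ = 0.3, and per-visit attendance p as shown in the table.

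**Model.** Attended visits per person are beta-binomial(m, p, ρ), with a = p(1−ρ)/ρ and b = (1−p)(1−ρ)/ρ.

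**Count.** Variance per person is m·p(1−p)·[1+(m−1)ρ]. For 50% v 70%:
- Control: 5 × 0.25 × 2.2 = 2.75. Telehealth: 5 × 0.21 × 2.2 = 2.31.
- Difference in means: 5 × 0.20 = 1.0 visit. SE = √((2.75 + 2.31)/20) = 0.503, so z = 1.988.
- Power = Φ(1.988 − 1.96) = 0.511.

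**Threshold of two, visits counted after randomisation.** For the control arm at 50%, a = b = 1.167:
- P(0) = 0.500 × 0.650 × 0.731 × 0.781 × 0.816 = 0.151.
- P(1) = P(0) × 5a/(b+4) = 0.171.
- P(≥2) = 1 − 0.151 − 0.171 = 0.678. The same steps at 70% give 0.866.
- SE under the null (pooled) = 0.133; SE under the alternative = 0.129.
- Power = Φ((0.188 − 1.96 × 0.1327)/0.1294) = 0.288.
- Relative efficiency is the squared ratio of the z values: (0.188/0.1294 ÷ 1.988)² = 0.53.

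**Results, m = 5, ρ = 0.3, n = 20 per arm.** If intake counts, one visit after randomisation meets the threshold.

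| Attendance per visit | Power, count | Share above cut (control v telehealth) | Power, cut | Rel. eff. | Share above cut if intake counts | Power, cut | Rel. eff. |
|---|---|---|---|---|---|---|---|
| 20% v 40% | 0.568 | 27% v 56% | 0.4346 | 0.78 | 48% v 76% | 0.445 | 0.80 |
| 30% v 50% | 0.511 | 42% v 68% | 0.372 | 0.73 | 64% v 85% | 0.319 | 0.60 |
| 50% v 70% | 0.511 | 68% v 87% | 0.288 | 0.53 | 85% v 95% | 0.185 | 0.30 |
| 60% v 80% | 0.568 | 78% v 93% | 0.258 | 0.40 | 91% v 98% | 0.147 | 0.19 |

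Counting the intake visit makes the loss larger from 30% v 50% upward. At 20% v 40% it makes almost no difference.

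**Range.** With m = 3, 5, 8 or 12, ρ = 0, 0.3 or 0.5, the four attendance pairs above, and intake counted or not (4 × 3 × 4 × 2 = 96 cases), the threshold had lower power than the count in all 96. Relative efficiency ran from about 0.00 to 0.94. At 20% v 40% with ρ of 0.3 to 0.5 it was 0.67 to 0.94.

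**The case against.** **The dichotomy is not firmly fixed.** The sentence goes on to a scheduled denominator, which could mean a proportion of visits. Logistic regression is only an example, and the article separately keeps the number and frequency of visits as a measure. A count model would fit the general wording about choosing a test. This stands to the extent that the loss is conditional on the yes/no being analysed. It does not remove the point, because the only definition in the analysis section is the two-visit threshold, and it matches neither a visit proportion nor the count named earlier.

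**The size is not established.** A reader might infer that most of the attendance information is lost and that both arms sit near the ceiling. The documents do not support this. They give no attendance rates and no number of scheduled provider visits. With low attendance, plausible in a population the Background calls hard to reach, the threshold keeps much of the information and there is no ceiling. Five visits is a proxy, since the Control condition section describes treatment phased case by case.

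**A raw count has its own weakness.** It partly reflects how many visits were scheduled, and it includes the drop-ins allowed under Intervention condition. This stands, and is why the fix adds the proportion of scheduled visits attended.

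**The consequence is limited.** The outcome is secondary in Table 2, the trial is not powered for efficacy, the arm comparison is exploratory, and visit records are kept, so nothing is irretrievably lost. This stands and sets the priority. Power serves here only as a measure of relative precision, which the article does claim.

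**Conclusion.** The concern holds in a conditional form. Appointment adherence is defined by a low threshold over a denominator that does not fit it, while the article records attendance and names the visit count as a measure. If the arms are compared on the yes/no, information already in hand is discarded.

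The direction is robust, since the count was more efficient in every case examined. The size is not known. In the central case (five visits, ρ = 0.3, 20 per arm), the power given up is about 13 points at 20% v 40% attendance (57% − 43%, before rounding 56.8 − 43.5), 22 points at 50% v 70% (51.1 − 28.8) and 31 points at 60% v 80% (56.8 − 25.8). All of these rest on assumed attendance, visit number, correlation and 1:1 allocation. Whether either arm would approach a ceiling cannot be told from the documents. Priority is modest.

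**What to change.** Under Sample size and planned data analyses:
- Make the arm comparison the number of attended buprenorphine provider visits, at the clinic or by library telehealth, per randomised participant, counted after randomisation over the 12 weeks. This also settles that the intake visit is excluded.
- Estimate a rate ratio (negative binomial or quasi-Poisson) or a mean difference, with a 95% CI.
- Report the proportion of scheduled visits attended as a supporting summary, because schedules are individual and drop-ins are allowed.
- Keep two or more visits as a descriptive percentage by arm.

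The cost is about one sentence. No new data are needed, because attendance is already taken from the clinic record, and no clinical procedure changes. A rate ratio or mean difference is slightly harder to present than a percentage, and the count must be read beside the scheduled-visit proportion.

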#### Feasibility of the telehealth intervention

Proportion of telehealth intervention arm participants who complete at least one telehealth visit appointment at the library.Proportion of scheduled visits with the buprenorphine provider that participants attend via telehealth at the library.We will also document any barriers to telehealth that arise (e.g., internet connection issues).

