### Intervention condition

In the intervention group, participants are scheduled for regular appointments at the FJV Health Center, which they attend via telehealth at the library. However, they can also access telehealth with FJV Health Center at unscheduled times. Unscheduled drop-in appointments is a standard available option for FJV Health Center patients and can be extended to library telehealth. The ability of unhoused participants to keep their regular buprenorphine appointments, whether in-person or by library telehealth, is a process measure for the study.

In some situations, participants can be interviewed outside of the library, if a room is not available in the library or the participant has too many belongings to bring inside the library.

Efforts are made to keep appointments private in locations not within hearing distance of others. The libraries have a computer tablet on a telehealth floor stand in a private study room for this study. The libraries make the computer tablet available on a heavy platform (to prevent theft) that can be placed in a library study room. The tablet is an alternative that removes barriers for patrons without ID cards who would otherwise need an ID card to check out library laptops.

FJV medical providers follow standard of care practice (whether in-person visit or over telehealth) to provide medication adherence counseling, medication education (e.g., how to take buprenorphine), information about what to expect, appointments, and treatment goals (e.g., relapse prevention, health/mental health referrals). Researchers help make follow-up appointments with the FJV Health Center for both the control and telehealth library groups, and research or library staff can also assist patrons with logging on to their telehealth appointments.

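### Appointment adherence is divided by the number scheduled, a post-randomization count with no clear unit that is not reconciled with the promised per-randomization analysis

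*Protocol article*

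**What the plan says.** All of the rule stands in one section of the Protocol article, Sample size and planned data analyses.

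- **Denominators.** Uptake, adherence and appointment adherence "will be divided by the number prescribed and scheduled, respectively". Read in order, uptake and adherence take the number prescribed, and appointment adherence takes the number scheduled. The appointment numerator is whether a person attended at least two buprenorphine appointments, taken from clinic records.
- **Comparison.** The next paragraph states: "We will conduct an intent-to-treat (i.e., per-randomization) analysis following CONSORT guidelines to explore potential differences between study arms on the outcomes". The models are unadjusted, with arm as the exposure, for example "logistic regression with binary outcomes".
- **Status.** The trial is described as "though not statistically powered to assess efficacy on primary outcomes". Its adherence estimates are nevertheless meant to feed the power calculations of later efficacy trials.

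Other sections bear on when each count arises:

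- Randomization and intake: participants are randomized after a clinic provider confirms eligibility for buprenorphine.
- Intervention condition: researchers help both arms make follow-up appointments, and of the telehealth arm it says "they can also access telehealth with FJV Health Center at unscheduled times".
- Strengths and limitations of the study design: drop-in visits are open to both arms.

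**The concern.** A per-randomization comparison keeps everyone in the arm to which they were allocated. A denominator that forms during follow-up does not. Having a follow-up appointment on the books is partly a result of staying in care, which the intervention is meant to improve. If fewer people are ever scheduled in one arm, dividing by the number scheduled raises that arm's rate because its losses have been removed.

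Two further defects apply to the same ratio. A drop-in visit can count as attended with no scheduled entry to match it. And a yes/no per person cannot sensibly be divided by a number of visits, yet the text does not say whether persons or visits are counted.

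What is at stake is the effect size estimate, which is a main product of this pilot. Table 2 lists appointment-keeping as secondary, but the section on feasibility of the RCT names clinic visits among the measures of the primary outcomes and includes appointment adherence in the hypothesis.

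**Working it through.** The article gives no event rates, scheduling rates or allocation ratio, so it has no figure of its own to reproduce here. From the target of 40, I assume 20 per arm. All event and scheduling counts below are also assumptions.

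**1. Order of events.** Intake visit and eligibility check, then randomization, then follow-up scheduling. The number scheduled for follow-up is therefore fixed only after randomization, whether it counts persons or visits. The number prescribed is different: Study setting and Conceptualizing each aspect of the intervention tie the first prescription to the clinic's in-person visit, which precedes randomization.

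**2. Appointment adherence, counting persons.** Assume 12 of 20 telehealth and 9 of 20 control participants attend at least twice.

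Per randomization: 12/20 - 9/20 = 60% - 45% = +15 points.

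Divided by persons scheduled, 12/(20 - a) - 9/(20 - b), where a and b are the numbers never scheduled in the telehealth and control arms:

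| a | b | Telehealth | Control | Difference |
|---|---|---|---|---|
| 0 | 0 | 12/20 = 60% | 9/20 = 45% | +15 points |
| 2 | 2 | 12/18 = 67% | 9/18 = 50% | +17 points |
| 2 | 6 | 12/18 = 67% | 9/14 = 64% | +2 points |
| 0 | 6 | 12/20 = 60% | 9/14 = 64% | -4 points |
| 2 | 8 | 12/18 = 67% | 9/12 = 75% | -8 points |

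The sign reverses only when 12/(20 - a) < 9/(20 - b), that is, when (20 - b)/(20 - a) < 9/12 = 0.75. With a = 0 this needs b of at least 6, since 14/20 = 0.70. With a = 2 it needs b of at least 7, since 13/18 = 0.72. When a = b the sign cannot change.

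**3. Appointment adherence, counting visits.** Suppose 12 people stay with 6 scheduled visits each, and 8 leave with 1 each: 12 × 6 + 8 × 1 = 80 visits. Twelve successful persons over 80 visits is 15%, against 12/20 = 60% of persons. If each of the 12 attended 5 visits, the attendance ratio is 60/80 = 75%. These are three different quantities, and the text does not say which is meant.

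**4. Uptake.** Assume 12 of 20 in an arm take up treatment. Everyone prescribed: 12/20 = 60%. With 1, 2 or 4 never prescribed: 12/19 = 63%, 12/18 = 67%, 12/16 = 75%. Screening and enrollment, and Randomization and intake, require confirmed eligibility before randomization but not a written prescription. The two counts can therefore differ, though the tie between intake and first prescription suggests only slightly.

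**The case against.** The strongest defence is that the division only describes rates, while the arm comparison is separately declared to be an "intent-to-treat (i.e., per-randomization) analysis following CONSORT guidelines". The models are never said to exclude anyone. That stands as far as it goes: a reader might infer a flat contradiction, and the text does not establish one. But the section does not label the ratios as descriptive. It attaches these denominators to the outcomes and then models each outcome, so an analyst could follow either sentence.

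A reader might also infer that people who leave care drop out of the primary-outcome denominators, or that someone who fills one prescription of one would score better than someone who fills five of six. Neither is supported. The first prescription belongs to the visit before randomization, and later dropouts remain among the persons prescribed. Uptake and adherence are defined per person in Table 2, adherence by more than one positive screen, so fills over prescriptions is not the outcome.

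Finally, the sign reversal rests on assumed counts. Researchers help schedule in both arms and contact everyone, including those who miss appointments, so the imbalance may be small. Drop-in visits supplement scheduled ones and do not replace them. These points limit the likely size, but they do not make the number scheduled a baseline count.

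**Conclusion.** The point holds for appointment adherence. Its stated denominator arises after randomization, can differ by arm, does not fit drop-in visits and has no stated unit. It is not reconciled with the per-randomization analysis in the same section. With 20 per arm and the assumed counts, the difference moves from +15 points to between +17 and -8. This shows that distortion, and in an extreme case reversal, is possible; it is not a forecast.

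For uptake and adherence the point is minor. If the number prescribed means persons given a prescription at intake, it is close to the number randomized and may differ slightly because only eligibility is confirmed beforehand.

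Severity is moderate. The trial is an unpowered pilot, its comparisons are exploratory, and the clearest effect is on a measure that Table 2 lists as secondary.

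**What to change.** Amend the denominator sentence in Sample size and planned data analyses to state that:

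- for the arm comparison of uptake, adherence and appointment-keeping, each a yes/no per person, the denominator is all randomized participants in each arm;
- participants never prescribed or never scheduled stay in the denominator and count as not meeting the corresponding outcome, unless drop-in visits bring a never-scheduled participant to the required two;
- attended provider visits count whether scheduled or drop-in;
- attended/scheduled and filled/prescribed are reported only as descriptive process ratios, labelled as such, with the unit (persons, visits or prescriptions) named.

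The telehealth-arm feasibility metric, "Proportion of scheduled visits with the buprenorphine provider that participants attend via telehealth at the library", is already a process ratio of this kind and can stay. How to handle missed urine screens is a separate missing-data question that this change need not settle.

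The cost is a few sentences. Consent to clinic records and to the state dispensing database is obtained at screening, so visits and fills can be sought for everyone randomized. The downside is that reported rates may be slightly lower.
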